**Fig. 1 Fig1:**
[figure not shown]
Schedule of enrolment, interventions and assessments of the SUNDRO trial

#### Experimental design aim 2

In order to investigate whether vitamin D supplementation might improve clinical and embryological parameters, we will use our electronic dataset to compare with appropriate statistical tests all of the variables that are routinely collected in IVF cycles. The main variables that we will consider in order to discover possible effects of vitamin D supplementation on the clinical outcome of the IVF cycle are: rate of cancelled cycles, number of available oocytes, units of FSH administered per retrieved oocyte (they are related to the rate of appropriate response of the patients to the stimulation protocol), number of good quality embryos on the day of embryo transfer as evaluated according to the Istanbul Consensus (it is related with the quality of gametes) [14], implantation rate of transferred embryos (it is related to the quality of embryos and endometrium), delivery rate and obstetric outcomes.

#### Experimental design aim 3

A subgroup (*n* = 50) of good-prognosis cases and controls will be recruited among randomized patients for collection and analysis of biological samples as described below.

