### Aim

The present trial is aimed at determining the benefits of vitamin D supplementation in improving cumulative clinical pregnancy rate in women undergoing IVF. In particular, the three main aims of the study are as follows:
Aim 1: To determine the potential benefits of vitamin D supplementation in improving cumulative clinical pregnancy rate in women undergoing IVF.Aim 2: To investigate whether vitamin D supplementation might improve clinical and embryological variables such as: number of cancelled cycles, number of available oocytes, number of good quality embryos, units of FSH administered per retrieved oocyte, implantation rate of transferred embryos.Aim 3: To investigate the effect of vitamin D supplementation on oocyte and endometrium quality at a molecular level through a comparative analysis between treated and untreated patients based on the analysis of cumulus cells, follicular and endometrial fluids.

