### Interventions

#### Experimental design aim 1

Recruited women will be given the drug (either 600,000 IU of 25-OH-vitamin D or placebo in a single oral administration) at the time of randomization, thus 2–12 weeks prior to oocyte retrieval and managed according to a standardized clinical protocol of ovarian stimulation with in vitro fertilization (fresh cycle). Administration of the drug/placebo will be performed by the physician in order to guarantee a compete adherence to the protocol. No dose changes are foreseen. Patients will be asked to avoid further consumption of vitamin D after randomization.

Women whose cycle will be cancelled will not be excluded (intention to treat analysis). A specific software will establish the randomization list. Sun exposure during the study period will be recorded but it will not be a reason for drop-out. Serum 25-OH-Vitamin D will be reassessed at the time of hCG administration or, if the cycle will be cancelled, at the time of the decision to interrupt the treatment. The quantitative detection of total serum 25(OH) D levels will be performed using a commercially available kit based on a chemiluminescence technology (DiaSorin) with intra- and interassay coefficients of variations equal to 10 and 15%, respectively.

Patients will be treated according to standard IVF protocols as described elsewhere [12, 13]: since neither the clinicians nor the recruited women will be aware about vitamin D dosage, clinical management of ovarian stimulation will not be conditioned by the study.

In case of supernumerary oocytes or embryos deriving from the fresh cycle, the subsequent embryo transfer using thawed embryos or oocytes will be considered for the study outcome if performed within 4 months from oocyte retrieval and 25(OH) D serum levels will be reassessed.

Serum hCG assessment to detect pregnancy will be performed at + 14/+ 16 days after hCG administration. If positive, women will undergo a transvaginal sonography 3 weeks later.

Clinical pregnancy (primary outcome) is defined as the presence of at least one intrauterine gestational sac with viable foetus.

Dates of the study: 27/06/2016–26/06/2019

A schedule of enrolment, interventions and assessments of the study protocol is reported in Fig. 1.

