### Sample size calculation

The sample size was calculated according to Kane [19] based on the following assumptions:

1) the primary outcome is the cumulative clinical pregnancy rate (CPR) per started cycle; 2) expected CPR in the deficient population 20% [7], 3) expected CPR in the supplemented population 30% [7], 4) expected proportion of women with insufficient serum vitamin D (< 30 ng/ml): 90% [20], 5) Type I and II errors of 0.05 and 0.20, respectively. Under these assumptions, a sample size of 300 randomized women per arm will allow us to detect with sufficient statistical power (*p* < 0.05) an absolute difference ≥ 10% in the CPR rate between the two groups using the chi-squared test.

Considering that 10% of recruited women are expected to have serum vitamin D levels ≥30 ng/ml (therefore they will not be randomized) and considering a dropout rate of 5%, it has been decided to recruit 700 women to reach the number of 600 required subjects. The full formula used for sample size calculation is provided as an additional figure (see Additional file 2).

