Dosage of supplementation was based on previous data showing that a single 600.000 IU dose of cholecalciferol is able to rapidly increase serum 25(OH) D levels and to maintain adequate levels up to 90 days after administration in young subjects, including patients with severe vitamin D depletion. The proposed dosage is indeed considered safe since it gives peak levels well below the widely accepted toxic blood levels of 200 ng/ml [21, 22]. Of note, the single dose administered in-office by the physician guarantees a total adherence to treatment. However, given the lack of causal relationship between vitamin D levels and IVF outcomes and the risk of excessive vitamin D serum levels, patients will be asked to avoid further consumption of vitamin D after randomization. Moreover, at a molecular level, our analysis can provide preliminary data on reproductive cells that can be influenced by circulating vitamin D levels (endometrium, follicle, oocyte cumulus-oocyte complex). Whether the effect of vitamin D in human reproduction is mediated at ovarian, endometrial or both levels represents a matter of controversy. According to our prospective cross-sectional study aiming at investigating IVF outcomes in women with deficient 25(OH) D level, the number of top quality embryos and, as a consequence, the rate of women reaching the stage of blastocyst transfer was higher in women with sufficient levels of serum 25(OH)D. The chances of embryo implantation were also enhanced supporting the idea that the impact of the compound might be exerted in both the reproductive tissues [7]. Disentangling the potential role of vitamin D in the endometrium is particularly relevant given the key role of uterine factors in determining the outcome of IVF treatment, the significant gaps in our knowledge of mechanisms underlying endometrial-embryo asynchrony and most of all, the lack of relevant modifiers of endometrial receptivity status [23]. Also of particular note, there is growing and consistent evidence that vitamin D supplementation may improve birth outcomes and prevent some relevant obstetrics complications. According to a recent systematic review of the randomized studies on vitamin D supplementation, the compound increases mean birth weight of 58.33 g (95%CI 18.88–97.78 g) [24]. Moreover, a lower risk in pre-eclampsia was observed in those women receiving vitamin D supplementation, especially if they received also calcium [25].

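### The Aim 2 count of good-quality embryos is taken on a day that itself depends on embryo quality, so the arms may be compared at different developmental stages

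*Protocol article*

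**What the plan says.** Under Interventions, Experimental design aim 2, one of the main variables is the "number of good quality embryos on the day of embryo transfer as evaluated according to the Istanbul Consensus". The same sentence explains its purpose: "it is related with the quality of gametes". The Aim section lists the endpoint without any day: "number of cancelled cycles, number of available oocytes, number of good quality embryos, units of FSH administered per retrieved oocyte".

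The Discussion describes the group's earlier study, in which, among women with sufficient vitamin D, "the number of top quality embryos and, as a consequence, the rate of women reaching the stage of blastocyst transfer was higher".

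The article does not give its own rule for choosing the day of transfer: "Patients will be treated according to standard IVF protocols as described elsewhere". It keeps cancelled cycles in the analysis: "Women whose cycle will be cancelled will not be excluded (intention to treat analysis".

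**The concern.** An outcome should be read at a time that the treatment cannot move. Here the time of reading is the transfer day. By the protocol's own account, women with more top-quality embryos more often reach blastocyst transfer. A woman who does well is then counted later, after some of her embryos may no longer rate as good; a woman who does poorly is counted earlier, before that loss. If supplementation improves embryos, the two arms are counted at a different mix of stages because of the treatment effect.

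This is a stated rule, not a detail left for another document. Blinding does not remove the problem: embryologists who do not know the allocation still see the embryos, and the dependence runs through embryo quality.

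What is at stake is the reading of one mechanism. The first hypothesis in the Background names oocyte and embryo quality as one of two routes by which vitamin D may act, and this endpoint is a routine clinical measure of that route.

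**Working it through.** **Figures in the plan.** No figure is stated for this endpoint. The only one nearby is 300 per arm for the primary outcome, with "Type I and II errors of 0.05 and 0.20, respectively". For 20% vs 30%, two-sided: n = (1.96·√(2·0.25·0.75) + 0.8416·√(0.20·0.80 + 0.30·0.70))² / 0.10² = (1.200 + 0.512)² / 0.01 ≈ 294 per arm. Power at 300 is about 0.81. That figure reproduces and plays no part in what follows.

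**Model for the endpoint (all inputs are assumptions; the article gives none).**
- Good embryos per woman at an early fixed day: mean 2.0 vs 2.5, or 3.0 vs 3.75, a true ratio of 1.25. Distribution Poisson, or negative binomial with size 3.
- Women with at least t good embryos (t = 3 or 4) go on to blastocyst stage; the others are counted early.
- Each good embryo is still rated good at blastocyst stage with probability s.
- Mean count on transfer day = Σ(k<t) k·P(k) + s·Σ(k≥t) k·P(k).

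**One case by hand** (Poisson, 2.0 vs 2.5, t = 3).
- Placebo: the part below 3 is 1(0.2707) + 2(0.2707) = 0.812; the rest is 2.0 − 0.812 = 1.188.
- Vitamin D: the part below 3 is 1(0.2052) + 2(0.2565) = 0.718; the rest is 2.5 − 0.718 = 1.782.
- s = 0.4 in both arms: 0.812 + 0.4(1.188) = 1.287 vs 0.718 + 0.4(1.782) = 1.431. Ratio 1.11.
- s = 0.9 in both arms: 1.881 vs 2.322. Ratio 1.23.
- s = 0.5 placebo, 0.6 vitamin D: 1.406 vs 1.787. Ratio 1.27.

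**Range over both distributions, both pairs of means and both thresholds** (true ratio 1.25):

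| s, placebo / vitamin D | Ratio seen on transfer day |
|---|---|
| 0.4 / 0.4 | 1.08 to 1.16 |
| 0.5 / 0.5 | 1.12 to 1.19 |
| 0.6 / 0.6 | 1.16 to 1.20 |
| 0.8 / 0.8 | 1.21 to 1.23 |
| 0.9 / 0.9 | 1.23 to 1.24 |
| 1 / 1 | 1.25 |
| 0.5 / 0.6 | 1.22 to 1.37 |
| 0.6 / 0.7 | 1.24 to 1.37 |

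**Second check, by simulation** (gamma-Poisson counts, control mean 3, true ratio 1.20, 300 per arm). With equal s the transfer-day ratio is 1.11 to 1.14 at s = 0.4 and 1.18 to 1.19 at s = 0.8. Power falls from about 0.70 at a fixed day to 0.42 to 0.45 at s = 0.4, 0.52 to 0.55 at s = 0.5 and 0.67 at s = 0.8. If s rises from 0.5 to 0.6 with treatment, the ratio is 1.27 to 1.33, above the true 1.20. If treatment changes neither the count nor s, the arms do not differ, so the rule creates no difference in that case.

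**The case against.** A reader might infer that the endpoint is biased against vitamin D. The documents do not say so. That reading needs two further assumptions: that fewer embryos rate as good at blastocyst stage, and that the loss is the same in both arms. The second fits poorly with the trial's own hypothesis, since better embryos may also survive better. The table shows that a modest gain in survival can cancel or reverse the shortfall. This objection stands, and the point is worded accordingly.

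A reader might also quote the loss on the absolute scale: under equal s of 0.4 to 0.6 only 22% to 60% of the true difference in means remains. Much of that is a change of scale. If every woman in both arms were counted at blastocyst stage with s = 0.4, only 40% of the difference would remain, with the ratio still at 1.25. The ratio is the fairer measure.

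Nor does the working show that a real benefit would be reversed in sign. In a cruder calculation where the share reaching blastocyst rises from 30% to 50%, a true ratio of 1.10 becomes 1.10 × (0.5 + 0.5·0.4)/(0.7 + 0.3·0.4) = 0.94 at s = 0.4 and 1.00 at s = 0.6. That takes a large shift in stage.

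Other limits also stand. The link between quality and stage comes from an earlier observational study, and this trial's transfer policy is left to cited sources. The value given to a woman without a transfer may be set in the full protocol or analysis plan, so its absence here is not counted against the article. Aim 3 also looks at oocyte quality, through granulosa-cell expression and follicular-fluid markers, so this is not the only such measure. None of this supplies a common time of assessment.

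**Conclusion.** The point holds in a limited form. The stated rule ties the time of counting to embryo quality, and the Discussion supplies the mechanism by which the arms could then differ in stage. Size and direction rest on assumptions. Under equal loss, a true 25% gain would show as about 8% to 24% for survival between 0.4 and 0.9, with no distortion at 1. Under better survival with treatment, it could show as up to about 37%. A null result could therefore hide a gain in early embryo quality. A positive one would point to some effect on embryos, but its size, and whether it lies in early quality or later survival, could not be read off. The endpoint is secondary; the primary outcome and the sample size are not touched. It should be corrected because the remedy is simple.

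**What to change.** Redefine the endpoint as the number of good-quality embryos at one fixed time after insemination, the same for every woman and earlier than the decision on transfer day, scored by the Istanbul criteria for that stage. Analyse it per randomised woman whether or not a transfer follows, with 0 where no embryo exists. Report blastocyst formation or stage at transfer as a separate outcome.

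The cost is a one-sentence change of definition, with no change to patient management. It assumes that earlier-stage scores are in the routine dataset. That is plausible, because Aim 2 draws on routinely collected variables and the Discussion implies that embryos are graded before the stage of transfer is settled, but it should be confirmed at both centres. The small downside is that later development leaves this endpoint and is reported on its own.

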### Data collection and analysis

An electronic dataset will be filled (SPSS ver. 20, IBM).

All data will be recorded with paper case report forms and entered electronically at both participating sites using a common dataset. Original study forms will be stored in numerical order and stored in a secure and accessible place for 30 years after study completion. A biostatistician will perform quality control before data analysis, including check for double data entry and range for data values. Missing data will be included in the analysis using specific modern imputation methods.

Statistically significant differences will be determined using Fisher’s exact test, chi-squared test, Student’s t test or the Wilcoxon test, as appropriate.

An interim analysis (315 randomized completed cycles) of clinical pregnancy rates will be performed in order to highlight unforeseen or higher-than-expected effects of vitamin D supplementation. According to the Haybittle–Peto boundary rule, the statistical significance for deciding to stop the trial is set to *p*-value < 0.001 [18]. Results of the interim analysis will be available to all medical and laboratory staff. The steering committee decides on the continuation of the trial and will report to the involved ethics committees.

In accordance with national guidelines, the main outcome will be collected for every woman in order to complete their clinical charts. Since the main outcome is the clinical pregnancy rate as (defined as the presence of at least one intrauterine gestational sac with viable foetus), it has to be noted that its evaluation is highly standardized and fully objective. Moreover, according to legal requirements and standard clinical protocols, secondary outcomes related to the evolution of pregnancies will be easily collected through usual methods and reminders for contacting patients.

Given the study design, protocol adherence is foreseen to be complete. However, data will be analysed according to the “intention to treat” analysis.

Since the clinical trial is designed as minimal risk a formal committee for data monitoring is not foreseen.

Electronic monitoring of the datasets will be performed by two independent physicians every 3 months during recruitment focussing on: completeness of the data, eligibility criteria, date of randomization, treatment assignment, adverse events and endpoints, signed informed consent.

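### Implantation is expressed per transferred embryo, but the named tests need independent observations; FSH dose per oocyte has no value for women without oocytes (minor, secondary outcomes only)

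*Protocol article*

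**What the plan says.** All references are to the protocol article.

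- **Outcomes.** Experimental design aim 2 lists "implantation rate of transferred embryos (it is related to the quality of embryos and endometrium", and the Aim section names the same rate. It also lists "units of FSH administered per retrieved oocyte (they are related to the rate of appropriate response of the patients to the stimulation protocol". Cancelled cycles and the number of available oocytes are separate items on the same list.
- **Tests.** Experimental design aim 2 will "compare with appropriate statistical tests all of the variables that are routinely collected in IVF cycles". Data collection and analysis gives the methods: "Statistically significant differences will be determined using Fisher’s exact test, chi-squared test, Student’s t test or the Wilcoxon test, as appropriate". No method for correlated observations is named, and the unit of analysis for implantation is not stated.
- **Several embryos per woman.** The Interventions section, under aim 1, adds that "the subsequent embryo transfer using thawed embryos or oocytes will be considered for the study outcome if performed within 4 months from oocyte retrieval". A woman can therefore have a fresh and a thawed transfer, and a single transfer may involve more than one embryo.
- **Analysis population.** The Interventions section also states: "Women whose cycle will be cancelled will not be excluded (intention to treat analysis". Data collection and analysis repeats the intention-to-treat principle.
- **Randomisation.** Allocation is 1:1 by woman, stratified by centre.

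**The concern.** There are two separate problems, both in Aim 2.

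**Implantation.** Embryos from the same woman share her uterus, her oocyte source and her vitamin D status, so their outcomes are likely to be positively correlated. A test that counts each embryo as an independent observation then overstates the information in the data, and its p-values and confidence intervals are too optimistic. The wording that tests will be chosen as appropriate selects within a list of four, none of which handles embryos clustered within women. The rate also exists only for women who reach transfer, a subgroup formed after randomisation.

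**FSH per oocyte.** The ratio has a zero denominator when a cycle is cancelled before retrieval or the retrieval yields nothing. Those women cannot enter the comparison unless a rule is set, yet the article says cancelled cycles are kept. Cancellation and oocyte number are themselves outcomes that vitamin D is hypothesised to change, so dropping these women would select on something the treatment may affect.

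The article reads these variables as markers of ovarian response, gamete quality and embryo or endometrial quality. Its Discussion took better implantation in the group's earlier study as support for an effect in both reproductive tissues. An overconfident implantation result would feed that kind of conclusion.

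**Working it through.** **1. The plan's own figure.** The article gives no calculation for Aim 2. Its only sample size is for the primary outcome: 20% against 30%, type I error 0.05, power 80%, 300 per arm. With the two-sided pooled formula,

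n = [1.96·√(2·0.25·0.75) + 0.842·√(0.20·0.80 + 0.30·0.70)]² / 0.10² ≈ 293.2, rounded up to 294 per arm.

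Power at 300 per arm is 80.9%. The figure reproduces. The primary outcome is a yes/no result per woman, so clustering of embryos does not touch it.

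**2. Inputs for the implantation check.** The article gives neither the number of embryos per woman nor the within-woman correlation. Both are assumed here:

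- 20%, 50% or 80% of women contribute two embryos and the rest one;
- correlation ρ runs from 0.05 to 0.5.

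**3. Formulas.** With m embryos per woman, the design effect is DE = 1 + ρ·(Σm²/Σm − 1). The real two-sided error of a per-embryo test at nominal 5% is 2·[1 − Φ(1.96/√DE)].

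For 50% with two embryos, the average of m is 0.5·1 + 0.5·2 = 1.5 and the average of m² is 0.5·1 + 0.5·4 = 2.5. So Σm²/Σm = 1.667, and at ρ = 0.3, DE = 1 + 0.3·0.667 = 1.20.

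| Women with two embryos | ρ | DE | Real type I error |
|---|---|---|---|
| 20% | 0.05 | 1.02 | 5.2% |
| 20% | 0.5 | 1.17 | 7.0% |
| 50% | 0.1 | 1.07 | 5.8% |
| 50% | 0.3 | 1.20 | 7.4% |
| 80% | 0.05 | 1.04 | 5.5% |
| 80% | 0.5 | 1.44 | 10.3% |
| none (one embryo, once) | any | 1.00 | 5.0% |

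**4. Check by simulation.** Beta-binomial data with 250 women per arm reaching transfer (assumed), a 20% rate and 20,000 runs gave 5.5% to 9.9% for ρ from 0.1 to 0.5, in line with the formula.

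**5. Width of intervals.** A correct interval is √DE times as wide as the naive one: √1.20 = 1.10 in the middle case and √1.44 = 1.20 at the top of the range.

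**6. FSH per oocyte.** No arithmetic is possible, because the article does not give the share of women expected to have no oocytes. Set side by side, one sentence keeps every woman with a cancelled cycle, and one outcome has no value for any such woman without a retrieval. The general promise to impute missing data does not close the gap, since a ratio with a zero denominator is undefined rather than missing.

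**The case against.** **No per-embryo test is fixed.** A reader might infer that implantation will be tested by an embryo-level chi-squared test and that the result will be wrong. The article does not say so. It leaves the choice of test open, and a per-woman proportion compared by Wilcoxon or t test, both named, would use independent units. This objection stands and makes the point conditional. It does not remove it: the rate is worded per embryo, the woman is nowhere stated as the unit, and no listed test suits embryos counted individually.

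**The detail belongs in an analysis plan.** An article may leave unit of analysis and clustering to a fuller document, and none is shown. That lowers the weight. What remains is a stated outcome and a stated list of tests that do not fit each other when read literally.

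**Larger inflation figures.** It is tempting to assume three embryos per woman from fresh plus thawed transfers. With ρ of 0.3 to 0.5, DE is then 1 + 2·0.3 = 1.6 to 1 + 2·0.5 = 2.0, and the error 12% to 17%. The documents do not support that range. It needs every woman to contribute three exchangeable embryos, including women who have already conceived. If thawed transfers follow only fresh failures (also an assumption), simulation at the same correlations gives about 9% to 12% for two fresh plus one thawed, 7% to 8% for one plus two, and 5% to 6% for one plus one. The rule on thawed transfers also stands under aim 1, so its application to implantation rate is itself an inference.

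**Poor responders are still visible.** Cancelled cycles and oocyte number are listed outcomes, so women without oocytes do not vanish from Aim 2. This is true and limits the harm, but the ratio itself still lacks a rule. A reader might also infer that the ratio loses exactly the poorest responders and is biased by a known amount. The article gives neither the reasons for nor the frequency of cancellation, so neither inference can be made.

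**Conclusion.** The point holds in conditional form and is minor. If implantation is tested per embryo with the named methods, significance is overstated. The real type I error is about 5% to 10% instead of 5%, under an assumed mix of one and two embryos per woman and a correlation of 0.05 to 0.5. The low end is negligible; the high end needs mostly double transfers and strong correlation. With one embryo transferred once per woman, or with a woman-level analysis, there is no inflation.

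The conflict over FSH per oocyte needs no assumption beyond some women having no retrieved oocytes, but its effect cannot be sized from the article. It would be wrong to conclude that the Aim 2 results are bound to be invalid.

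**What to change.** - **Implantation rate.** State the unit of analysis. If it is the embryo, use logistic GEE or standard errors clustered by woman. Alternatively, compute one proportion per woman and compare those with a listed test; this weights women rather than embryos equally. Say whether thawed transfers count. Label the result conditional on reaching transfer, and report the number of embryos transferred by arm.
- **FSH.** For all randomised women, report total FSH dose and number of oocytes retrieved, with 0 for cancelled cycles and empty retrievals. If the ratio is kept, label it conditional on at least one oocyte.

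**Cost.** A few sentences of analysis text and a little code, on data that IVF cycles routinely produce. Confidence intervals for implantation become slightly wider, about 10% in the middle case above. No change to the sample size or the primary analysis is needed.
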